### Who will take informed consent? {26a}

Informed consent documents will be obtained by the principal investigator at each subcenter. The participating consultant will explain the details of the informed consent document to the potential participants at each subcenter, and the principal investigators will obtain written permission from patients willing to participate in the trial.

### Additional consent provisions for collection and use of participant data and biological specimens {26b}

The subjects will be asked whether they agree to the use of their information. It should be noted that no biological samples will be collected in our study.

### Interventions

#### Explanation for the choice of comparators {6b}

After a 2-week run-in period, patients with stage 2 hypertension will be randomly divided into a treatment group and a control group, and they will receive Val/Aml plus TJT or Val/Aml plus TJT placebo for 4 weeks based on their lifestyle changes.

#### Intervention description {11a}

Participants in the treatment group will receive Val/Aml 80/5 mg once daily, combined with TJT tablets 1200 mg twice daily for 4 weeks. Participants in the control group will receive Val/Aml 80/5 mg once daily, combined with TJT placebo tablets 1200 mg twice daily for 4 weeks. TJT (production batch number 200603) and TJT placebo (production batch number 200604) were produced and packaged by the preparation center of the Affiliated Hospital of Shandong University of Traditional Chinese Medicine. After testing, the quality of the drug satisfied the requirements of TCM standards issued and implemented by the State Food and Drug Administration (SFDA), and the quality standards and testing methods of the placebo were consistent with those of the experimental drug. TJT has a composition of 300 mg/tablet; each tablet contains 230 mg *Uncaria angustifolia* extract and 70 mg *Semen Raphani* extract. The TJT placebo has a composition of 300 mg/tablet, each containing 136 mg yellow dextrin, 136 mg white dextrin, and 28 mg caramel. Val/Aml was purchased from Beijing Novartis Pharmaceutical Co., Ltd. (Beijing, China, Unified social credit code 9111000060001684X1).

#### Routine care

Routine care for participants in both groups during the trial will follow the Chinese Society of Hypertension’s 2018 Revision Guidelines for Prevention and Treatment of Patients with Cardiovascular and Cerebrovascular Disease, including reducing sodium salt intake, controlling body mass, quiting smoking, quiting drinking, reducing mental stress, and maintaining psychological balance and middle-intensity exercise.

#### Criteria for discontinuing or modifying allocated interventions {11b}

Discontinuation criteria are withdrawal of consent, subsequent occurrence of a suspension criteria criterion (e.g., use of prohibited drugs), lack of compliance, and medical problems for stopping the intervention.

#### Monitoring compliance

During each follow-up, the researcher will count the number of medicines distributed and recovered; record the number of medicines received, used, and returned by the subjects to measure the compliance; and record it in the CRF in time. Subjects with compliance rates lower than 80% will be considered to have low compliance.

#### Strategies to improve adherence to interventions {11c}

The researchers will improve patient compliance through regular follow-up, BP checks, and medication diary CARDS.

#### Relevant concomitant care permitted or prohibited during the trial {11d}

During the trial, patients will be requested to not use any additional herbal decoction or proprietary Chinese medicine, acupuncture, or other methods to treat hypertension.

#### Provisions for posttrial care {30}

According to the clinical use of *Uncaria rhynchophylla*, *Semen Raphani*, and other traditional Chinese medicine decoction pieces and Val/Aml, we do not expect serious adverse events due to our intervention.

### Outcomes {12}

#### Primary outcomes

The main functional variables in the study include the changes in msSBP and msDBP from baseline to week 4 (end point).

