**Methods:**

This randomized double-blind, placebo-controlled, multicenter trial will be conducted with a total of 288 participants with stage 2 hypertension at seven clinical trial centers. The stratified random method will be used, and the subcenter will be taken as the stratification factor. Eligible patients will be randomly assigned (1:1) into groups receiving either TJT or placebo three times daily for 28 days, both combined with Val/Aml 80/5 mg. The primary efficacy endpoint is the reduction in the mean sitting systolic blood pressure (msSBP) and the mean sitting diastolic blood pressure (msDBP) from baseline to week 4. Adverse events and laboratory test results will be monitored throughout the trial.

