#### Sample size {14}

The trial will check for superiority between the treatment group (treatment with Val/Aml and TJT) and the control group (treatment with Val/Aml and TJT placebo).

The calculation of sample size is based on the hypothesis of superiority and the method of comparing the two means. Assuming that the class I error rate is *α* = 0.05 and the class II error rate is *β* = 0.2, and based on a previous study [19], the test group DBP after treatment (*πc*) can be set as follows: DBP, 8.3 ± 5.53 mmHg, and the control group DBP after treatment (*πt*) can be set as follows: DBP, 6.3 ± 4.31 mmHg based on the effectiveness test sample size calculation formula:
$$ N=\left[2{\left({Z}_{1-\alpha }+{Z}_{1-\beta}\right)}^2{\delta}^2\right]/{\left({\pi}_T-{\pi}_c\right)}^2 $$

**δ**^2^ = (S1^2^ + S2^2^)/2; S1 and S2 are the standard deviations of the control group and treatment group, respectively; *α* = 0.05, *Z*_1−*α*_ = 1.96, *β* = 0.1, *Z*_1-*β*_ = 1.28, (*Z*_1 − *α*_ + *Z*_1 − *β*_)^2^ = 6.2. Then, each group needs a sample size of 120. The quality of the study will be strictly controlled during the trial. After considering the Good Clinical Practice (GCP) shedding rate (20%) and expanding the number of samples, we decided to recruit 288 patients in this trial, including 144 patients in the treatment group and 144 patients in the control group. The total number of cases in the two combinations will be 288: 144 in the treatment group and 144 in the control group.

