#### Principles and methods of statistical analysis

All analyses will be conducted with SPSS version 26.0 (IBM SPSS Inc., Armonk, NY, USA) or SAS version 9.4 (SAS Institute, Inc., Cary, NC, USA). The data analysis, data entry, and data management of each research center will be conducted in the Evidence-based Medicine Research Center of Shandong University of Traditional Chinese Medicine. Bilateral tests will be used for all statistical tests, with *P* < 0.05 being considered statistically significant (unless otherwise specified). The 95% confidence interval will be calculated. The quantitative index will include the calculation of the mean, standard deviation, median, minimum, and maximum. The classification index is described by the number of cases and percentages of each category. The two study groups will be compared using an independent two-sample Student’s *t* test. For categorical variables, a *χ*^2^ test will be used when appropriate. A Wilcoxon paired signed-rank test will be used for within-group comparisons.

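### Two primary outcomes (msSBP and msDBP), each tested at two-sided 0.05, with no stated rule on whether one or both must succeed, and a sample size based on DBP alone

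*Protocol article*

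**What the plan says.** The Primary outcomes section of the protocol article gives the pair: "The main functional variables in the study include the changes in msSBP and msDBP from baseline to week 4 (end point". The Methods paragraph of the abstract words it in the singular but with the same two components: "The primary efficacy endpoint is the reduction in the mean sitting systolic blood pressure (msSBP) and the mean sitting diastolic blood pressure (msDBP". Table 1 also lists msSBP/msDBP under primary outcomes.

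The section on principles and methods of statistical analysis says "Bilateral tests will be used for all statistical tests", "with *P* < 0.05 being considered statistically significant (unless otherwise specified". The between-group comparison is then set: "The two study groups will be compared using an independent two-sample Student’s *t* test". The article specifies no other level, order or alpha split for the two primary variables.

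Sample size {14} describes a superiority comparison of two means and takes its inputs from diastolic pressure only: "the test group DBP after treatment" is set at 8.3 ± 5.53 mmHg against 6.3 ± 4.31 mmHg in the control group. It arrives at 120 per group and recruits 144 per group. No SBP difference, SD or power appears anywhere in the article.

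**The concern.** Which result makes this a positive superiority trial is left open. With two primary variables and one blanket significance level, there are two ways to read the claim, and each has a problem.

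- **Either pressure suffices.** There are two chances to win at 0.05 each, so the overall false-positive rate exceeds 5%.
- **Both pressures are required.** The false-positive rate is controlled, but the power that matters is the power to win on both. The sample size section addresses only one of the two.

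If the choice is not fixed before unblinding, it can be made after the results are known. The main conclusion would then not be a clean 5% claim.

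**Working it through.** **Inputs from the document.** Two primary variables; two-sided 0.05 for each test (critical value 1.96); DBP means 8.3 and 6.3 mmHg, so a difference of 2.0; SDs 5.53 and 4.31; 120 per arm before dropout and 144 after. The means are labelled as DBP after treatment, but values of this size only make sense as reductions, and I read them so.

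**Inputs I had to assume.** The correlation between the SBP and DBP test statistics, and the power for msSBP. The document gives neither, so both are shown as ranges.

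**Step 1: the plan's own figure.** The stated formula is n = 2(Z₁₋α + Z₁₋β)²δ²/(difference)², with δ² = (5.53² + 4.31²)/2 = 24.58, so SD = 4.958.

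| Multiplier | n per arm |
|---|---|
| Two-sided 0.05, 80% power (7.85) | 97 |
| Two-sided 0.05, 90% power (10.51) | 130 |
| One-sided 0.05, 80% power (6.18; printed as 6.2) | 76 |
| One-sided 0.05, 90% power (8.56) | 106 |

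None gives 120. The section opens with "Assuming that the class I error rate is *α* = 0.05 and the class II error rate is *β* = 0.2" but later uses β = 0.1, and (1.96 + 1.28)² is 10.5, not the printed 6.2. These are separate defects. They matter here only because they leave even the target power for DBP unclear. I therefore computed DBP power directly from the stated difference and SDs.

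**Step 2: DBP power on the stated inputs.** Power = Φ(2.0/SE − 1.96), with SE = 4.958 × √(2/n).

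- n = 120: SE = 0.640, 2.0/0.640 = 3.125, power = Φ(1.165) = 87.8%.
- n = 144: SE = 0.584, 2.0/0.584 = 3.423, power = Φ(1.463) = 92.8%.

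The 144 figure applies if everyone randomised is analysed without loss of information, as under ITT with LOCF. The 120 figure is the plan's number before dropout.

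**Step 3: false-positive rate if either pressure suffices.** At zero correlation it is 1 − 0.95² = 9.75%. Otherwise it is P(|Z₁| > 1.96 or |Z₂| > 1.96) for a bivariate normal with correlation ρ.

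| ρ (assumed) | 0 | 0.5 | 0.7 | 0.8 | 0.9 |
|---|---|---|---|---|---|
| Familywise error | 9.75% | 9.1% | 8.3% | 7.8% | 7.0% |

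**Step 4: power if both are required.** Joint power = P(Z₁ > 1.96 and Z₂ > 1.96), with DBP power from step 2. Ranges run over ρ from 0 to 0.8.

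| msSBP power (assumed) | Joint power, 120 per arm | Joint power, 144 per arm |
|---|---|---|
| 70% | 62–69% | 65–70% |
| 80% | 70–77% | 74–79% |
| 90% | 79–84% | 83–87% |

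Joint power can never exceed the smaller of the two separate powers. Which row applies cannot be found from the article.

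**The case against.** **The rule may be elsewhere.** How two primary variables combine is often set in the SAP, which is not shown, and the 0.05 level carries the qualifier "being considered statistically significant (unless otherwise specified". That stands to this extent: the missing rule is established for this article only. It does not remove the point. The article itself names two primary variables, gives a default level for all tests, and sizes one of them. A later SAP could add an order of testing, but the sample size section would still rest on no SBP assumptions.

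**The wording leans towards both.** The abstract uses a singular endpoint, and the two pressures are joined by *and*, never *or*. The control-rate outcome is also a joint threshold. A reader might infer from the blanket 0.05 that a win on either pressure is what the plan intends. The text does not say so, and the both-required reading is open. Neither passage states a success criterion, though, and the both-required reading moves the problem to the unsized SBP component.

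**The inflation is easily overstated.** A reader might infer an error rate near double the nominal 5%. That needs zero correlation, whereas the two pressures come from the same readings in the same patient. A range of 7% to 9% is the fairer statement, still above 5%.

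**A power shortfall is not shown.** A reader might infer that the trial is underpowered if both are required. The documents do not support that: with msSBP power of 90% and 144 per arm, joint power is above 80%. What is shown is that the power is unstated and cannot be derived.

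**Conclusion.** The point holds. As the article stands, the primary claim has either a familywise error above 5% or a power with no stated basis, depending on a choice the article does not make.

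The error figures rest on an assumed correlation but exceed 5% throughout the range shown. The DBP powers rest only on the stated difference and SDs. The joint powers are illustrations, because the msSBP power in them is assumed. The finding is an undefined success criterion and an unsized component, not a demonstrated inflation or a demonstrated loss of power.

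**What to change.** Before unblinding, state one error-controlling rule for the two primary variables in the outcomes and statistical methods sections. Either of these would do:

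- **Fixed sequence.** Test msDBP at week 4 first, at two-sided 0.05, because it is the only endpoint sized. Test msSBP at 0.05 as confirmatory only if msDBP is significant; otherwise report msSBP with its confidence interval as descriptive.
- **Both required.** Say that superiority needs both to be significant at two-sided 0.05, and give the SBP difference, SD, assumed correlation and resulting joint power.

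In either case, say in Sample size {14} that the sample size and power refer to msDBP only, unless SBP assumptions are added.

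The fixed sequence costs a few sentences and no extra patients. Its downside is that no confirmatory msSBP claim is possible if msDBP fails. Requiring both costs an added calculation and may show that power is lower than the DBP figure. Since recruitment has begun (57 patients at the time of the article), the rule should be recorded as a dated amendment made while treatment codes are still concealed. The DBP-first order rests only on which endpoint was sized, and that calculation itself needs correcting; another order or an alpha split would also control the error, if fixed in advance.

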#### Secondary outcomes

The following are the secondary outcomes:
BP control rate at week 4 (defined as msSBP/msDBP < 140/90 mmHg).To evaluate the improvement of symptoms, the TCM syndrome scoring scale [22] will be used for evaluation (Additional file 3). To determine the degree of symptom improvement, we will refer to the Guiding Principles for Clinical Research on New Chinese Medicines [23]. Efficacy index = [(points before treatment − points after treatment)/points before treatment] × 100%. Significant effect: efficacy index ≥ 70%. Effectiveness: efficacy index ≥ 30%. Invalid: efficacy index < 30%.Other results include blood lipids, blood glucose, urinary microalbumin, uric acid, homocysteine, and hypersensitive C-reactive protein. It should be noted that no biological samples will be collected in our study.In addition, patient compliance will be assessed by counting the number of unused tablets returned at the scheduled visit. Table 1 shows the timing for all outcome measures in the study.

**Table 1 Tab1:** Outcome measures

Domain	Measurement	Time (days)

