**Secondary outcomes**		
BP control rate	Defined as msSBP/msDBP < 140/90 mmHg	28
TCM syndrome scoring	TCM syndrome scoring scale will be used for evaluating the improvement of symptoms (Additional file 3).	0,28

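### The TCM symptom classes overlap as printed, so the effective rate can mean two things, and neither between-group test the protocol names adjusts for the day-0 score

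*Protocol article*

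**What the plan says.** Under Secondary outcomes, the protocol article defines an index relative to each patient's own starting score: "Efficacy index = [(points before treatment − points after treatment)/points before treatment] × 100" per cent. It then gives three grades, all in per cent: "Significant effect: efficacy index ≥ 70", "Effectiveness: efficacy index ≥ 30" and "Invalid: efficacy index < 30". The middle grade has no upper limit.

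Table 1 lists TCM syndrome scoring itself as a secondary outcome, on days 0 and 28: "TCM syndrome scoring scale will be used for evaluating the improvement of symptoms".

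Principles and methods of statistical analysis is generic. The two groups are compared by an independent two-sample t test. For categorical variables the rule is that a chi-square "test will be used when appropriate". The only Wilcoxon test named is the paired one, for within-group comparisons. No test is tied to the TCM outcome, and no baseline-adjusted analysis is named. Improvement of clinical symptoms is one of the stated objectives.

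**The concern.** Two things are at stake.

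- **Definition.** Every index of 70% or more satisfies both of the first two grades. One analyst may report as effective the patients from 30% to below 70%; another may report everyone at 30% or above. The text permits both, and they can give opposite impressions of the same data.
- **Efficiency.** The score is already scheduled at both time points. If the grades alone were compared by an ordinary chi-square, their order and the score itself would be set aside. If the score were compared by the named t test, the day-0 value would not be used as a covariate.

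**Working it through.** The document gives no figure for this outcome to reproduce. From it come the cut-points, the two-sided 5% level and 120 per group before dropout (Sample size section).

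**Overlap.** An index of 80% satisfies both ≥ 70 and ≥ 30. The three printed grades are therefore not mutually exclusive.

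**Assumed model (not in the document).** Day-0 score has mean 20, SD 5. Day-28 control score has mean 11, SD 5. The benefit is 1.75 points, with 120 per arm. The correlation ρ between day-0 and day-28 scores is 0.3, 0.5 or 0.7.

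**Effect of the two readings, ρ = 0.5.**
- Effective meaning 30% to below 70%: 62.1% control, 62.6% treated, power about 5%. Treated patients leave the middle grade about as fast as others enter it.
- Effective meaning 30% or above: 75.1% control, 85.7% treated, power about 54 to 57%.

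**Score analyses by formula.** Power ≈ Φ(1.75 / (s·√(2/120)) − 1.96), where √(2/120) = 0.1291.
- Day-28 score: s = 5. Then 1.75/0.6455 = 2.71 and Φ(0.75) ≈ 77% at every ρ.
- Score change: s = 5√(2(1−ρ)) = 5.92 / 5.00 / 3.87, giving 63 / 77 / 94%.
- ANCOVA: s = 5√(1−ρ²) = 4.77 / 4.33 / 3.57, giving 81 / 88 / 97%.

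**Simulated power (%), range over repeated runs of the same model.** Here ANCOVA adjusts for the day-0 score only, because centre was not modelled.

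| Analysis | ρ = 0.3 | ρ = 0.5 | ρ = 0.7 |
|---|---|---|---|
| Chi-square, ≥ 30% vs < 30% | 48 | 54–57 | 68 |
| Chi-square, three disjoint classes | 58 | 65–69 | 76–78 |
| Ordered (Wilcoxon) test on the classes | 68–69 | 75–78 | 84–86 |
| t test on the index | 74 | 85–86 | 94 |
| t test on score change | 61–63 | 76–78 | 93–94 |
| t test on day-28 score | 78 | 77 | 76 |
| ANCOVA | 81–82 | 87–89 | 96–97 |

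Within single runs, ANCOVA gains:
- 19 to 24 points over the three-class chi-square;
- 2 to 8 over the t test on the index;
- 3 to 20 over the t test on change;
- 3 to 21 over the t test on the day-28 score.

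The ordered test gains 7 to 11 points over chi-square on the same classes.

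**Second assumed model.** The index is generated directly, with SD 0.3 and control mean 0.4 or 0.5, and treatment shifts it by 0.3 or 0.4 SD.
- Chi-square: 43–44% and 69–70%.
- Ordered test: 54% and 78–79%.
- t test on change: 52–56% and 77–80%.
- ANCOVA: 60% and 84–85%.
- t test on the index: 62–63% and 86–87%.

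The gain of ANCOVA over chi-square is 15 to 16 points. The t test on the index is ahead of ANCOVA by 2 to 3 points, because here the effect acts on the index itself. With no effect, rejection is 4.5 to 5.3% throughout.

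**The case against.** A reader might infer that the protocol commits this outcome to an unordered chi-square test. It does not. The rule is generic and qualified: "For categorical variables, a *χ*^2^ test will be used when appropriate". A trend or row-mean-score form is not excluded, and a separate analysis plan may settle the choice of test. That objection stands.

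A reader might also infer that the score is collected but not meant for analysis. Table 1 lists the score as the outcome, and the generic t test could be applied to it. Score information is lost only if the classes alone are tested, which the text does not say. That stands too.

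Nor is a three-class chi-square shown to be the least sensitive option: in the first model a chi-square on the two-class effective rate has lower power at every correlation.

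Baseline is not ignored either, since the index divides by it. Dividing by baseline is not adjusting for it, though: a 6-point fall is 6/20 = 30% from a score of 20 but 6/24 = 25% from a score of 24, and the two patients are graded differently.

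Finally, the 30% line may be meant as a customary total-effective rate. That is plausible, but the article does not say so, and the ambiguity remains.

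**Conclusion.** The overlap is a fact of the printed text and is the firm part of this point: the effective rate has two permissible meanings, and under the first assumed model one hides a benefit that the other shows.

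The analysis part is an improvement to make, not an error. Both between-group tests named leave out adjustment for the day-0 score. The size of the gain depends on which analysis would otherwise be used:
- about 15 to 25 points of power over a three-class chi-square, across both assumed models;
- in the first model, about 2 to 8 points over a t test on the index, a small advantage that reverses in the second model;
- in the first model, about 3 to 21 points over a t test on score change or day-28 score.

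All these figures rest on assumed score distributions and show direction and rough size only. The outcome is secondary, and type I error is unaffected for any one test fixed in advance.

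**What to change.** - Print disjoint limits: ≥ 70%; ≥ 30% to < 70%; < 30%. Report the classes descriptively. If a rate for all patients at 30% or above is also given, label it as the total-effective rate.
- Name the day-28 TCM score, analysed by ANCOVA with day-0 score and centre (the stratification factor), as the analysis of this outcome.
- If the classes are tested, use an ordered test, such as a Wilcoxon rank-sum or proportional-odds test.

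This changes wording only and needs no new data, because the score is already scheduled on days 0 and 28. As recruitment has begun, date the change before unblinding. The small downside is that the headline becomes a score difference instead of the customary class rates, which remain as description.
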